Eligible participants will be provided with detailed study information and consent form via post or email, and scheduled to attend a baseline appointment upon providing study consent. At the baseline appointment, body mass, height and BMI will be measured to confirm eligibility. Participants will be recruited via rolling recruitment and randomly allocated to a 12-week prescribed and individualized energy restricted diet enriched with high carotenoid fruits and vegetables and EVOO; or, a 12-week prescribed and individualized energy restricted diet enriched with lower carotenoid fruits and vegetables and a polyunsaturated fatty acid (PUFA) based oil. Volunteers will be randomly assigned to either group following the completion of all baseline measurements. Allocation will be stratified by BMI (27–29.9 kg/m^2^; ≥30 kg/m^2^) using a random number, computer generated randomisation schedule generated and managed by a member of the research team. An overview of the recruitment method and randomisation process is provided in Fig. 1.

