### Data collection

The timeframe for this study will be 18 months, from 1 July 2016 to 30 April 2018. This timeframe includes the collection of all outcome measures and statistical analysis pertaining to this study**.** Assessment of all outcome measures (primary or secondary) will be conducted at baseline and Week 12. The primary outcome measure for this study will be ASM. Secondary outcomes will include body weight, FFM, FM, muscle strength, physical performance, physical activity and health related quality of life. Participants will also report to the clinic each fortnight for the duration of the study where they will be weighed and receive individual dietary counselling by an Accredited Practising Dietitian (APD).

In preparation for all outcome assessments, participants will present to the clinic after an overnight fast wearing light figure hugging clothing without metal zips, tags, or studs. Following the completion of all baseline assessments, participants will be provided with a 3-day food diary and commence a one-week ‘run-in’ period before beginning the 12-week intervention. During the ‘run-in’ week, participants will be instructed to consume their habitual dietary intake. Throughout this period, participants will be asked to record all food and fluid intake across three days (two consecutive weekdays and one weekend day). Upon completion of the ‘run-in’ week, participants will return to the weight management clinic (Week 0) where food diaries will be verbally cross-checked for completeness by an APD, and any ambiguities will be clarified. Participants will be re-weighed following completion of the ‘run-in’ week.

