^a^Depending on their allocation, participants will be asked to consume fruits and vegetables from the allocated list only

^b^Participants randomized to the high carotenoid plus EVOO group will be asked to consume 375 g/d of high carotenoid vegetables and 300 g/d high carotenoid fruit

^c^Participants randomised to the lower carotenoid plus PUFA oil group will be asked to consume 375 g/d of lower carotenoid vegetables and 300 g/d lower carotenoid fruit

All participants will receive individual dietary counselling by an APD and will be provided detailed instructions on how to maintain and record their daily dietary checklist. If any deviations are made from the prescribed quantities in the checklist, participants will be instructed to record this. All participants will be provided with a selection of recipes, reflecting the composition of the dietary protocol. In addition, all participants will be provided a list outlining the type and variety of fruits and vegetables required for consumption. If participants request mid-meal snacks between meals, they will be counselled on selecting high protein based options. Volunteers will return the checklists every fortnight and these will be discussed with the APD to clarify serving sizes and address any potential issues or problems with compliance toward the dietary protocol. As an additional measure of adherence to the dietary protocol, body weight will be recorded each fortnight for the duration of the study. All participants will be asked to maintain their habitual level of physical activity for the duration of the study. All individual consultations will last between 20 and 30 min in duration. To facilitate compliance, all participants will be provided with a sample fruit and vegetable hamper valued at $30AUD each fortnight for the duration of the study, reflecting the key fruits and vegetables specific to their group allocation. Participants randomized to the high-carotenoid fruits and vegetables, plus EVOO group will also receive EVOO for the duration of the study. All other food(s) prescribed in the energy restricted diet will be provided by the participant.

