### Power calculations, intention to treat and statistical analyses

This study was powered on the primary outcome of change in ASM. Based on data from a previous intervention assessing preservation of ASM during intentional weight loss in obese older adults [22] it was estimated that *n* = 56 participants would provide 80% power to detect a significant (*P* < 0.05, 2-sided) change in ASM between the two study groups of 0.9 kg ± 1.2 kg. Assuming an attrition rate of 30%, the target sample size will be *n* = 73 participants. All analyses in the proposed study will be performed using intention-to-treat analysis, with all randomised participants included in the final analysis irrespective of compliance.

Non–normally distributed variables will be logarithmically transformed before analysis. Where normality is not achieved, non-parametric methods for analyses will be used. Descriptive statistics will be presented for baseline characteristics, and independent sample t-tests or chi square analysis will be used to ensure that there are no significant differences between randomised groups. Paired t-tests will be used to identify whether outcome parameters change over time. After screening for assumptions related to multicollinearity, normality, linearity, homogeneity and reliability of covariates, analysis of covariance (ANCOVA) will be applied to identify differences between groups over time, with diet groups as the independent variable and outcome parameters as the dependent variable. Covariates will be determined using a correlation matrix to identify significant interactions between potential confounders. Analyses will be performed using SPSS for Windows 24.0 software (SPSS Inc., Chicago, IL, USA) with statistical significance set at *P* < 0.05.

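### The article promises to analyse everyone randomised, but the methods it names cannot use a participant without a Week 12 DXA, and it allows for 30% attrition

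*Protocol article*

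**What the plan says.** Four statements in the protocol article bear on this.

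- **Analysis set** (Power calculations, intention to treat and statistical analyses): all analyses are to be intention-to-treat, "with all randomised participants included in the final analysis irrespective of compliance".
- **Expected loss** (same section): "Assuming an attrition rate of 30%, the target sample size will be *n* = 73 participants".
- **Timing of outcomes** (Data collection): "Assessment of all outcome measures (primary or secondary) will be conducted at baseline and Week 12". Under Study design, participants and recruitment, "Volunteers will be randomly assigned to either group following the completion of all baseline measurements", so each randomised participant should have a baseline ASM. The value at risk is the one at Week 12.
- **Methods** (Power calculations, intention to treat and statistical analyses): paired t-tests for change over time and ANCOVA for the comparison of diets, with non-parametric alternatives where normality fails. No method is named for a missing Week 12 value, and no complete-case set is named either.

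The one measurement taken between baseline and Week 12 that could inform a missing ASM value is weight. The Dietary protocol section says that "body weight will be recorded each fortnight for the duration of the study".

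**The concern.** The article fixes three things: who is analysed (everyone randomised), how (methods that need a Week 12 value), and how many may be lost (30%). As written, they do not fit together. The qualifier about compliance deals with people who do not follow the diet. It does not supply an outcome for people who were not scanned.

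An analyst who followed the text literally in SPSS would obtain a complete-case result and report it as an analysis of all randomised participants. Readers would then credit the primary comparison with the protection of randomisation, which it would have lost in part. The loss could matter here because ASM change is studied during weight loss, and people who leave a weight-loss diet may differ in ASM change from those who stay. The arms also differ in one documented respect that could affect retention: the Dietary protocol section says that olive oil is supplied to the high-carotenoid arm, and that other foods are provided by participants.

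**Working it through.** **Inputs.** Difference 0.9 kg, with ±1.2 kg read as the SD ("change in ASM between the two study groups of 0.9 kg ± 1.2 kg"); two-sided 5% level; 80% power with 56 participants; 30% attrition; 73 randomised. The allocation ratio is not stated, so 1:1 is assumed.

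**1. The plan's own figures.**
- n per arm = 2 × (1.960 + 0.842)² × (1.2/0.9)² = 27.9, so 28 per arm and 56 in total. This matches. A t-based calculation gives 28.9, so 29 per arm and 58 in total.
- 56 × 1.3 = 72.8, so 73. This matches the stated target.

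**2. How many the named methods can use.** If all attrition means no Week 12 DXA, 73 × 0.70 = 51.1, so about 51 are analysed and about 22 are not.

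**3. Power.** Normal approximation: power = Φ(0.75 × √(n/2) − 1.96), where n is the number per arm and 0.75 = 0.9/1.2.

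| Participants with Week 12 ASM | n per arm | Normal | t-based |
|---|---|---|---|
| 56 (as planned) | 28 | 80.1% | 78.7% |
| 51.1 (30% of 73 lost) | 25.55 | Φ(0.72) = 76.4% | 74.8% |
| 73 (none lost) | 36.5 | Φ(1.24) = 89.3% | 88.5% |

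Compared like with like, 30% loss costs about 4 percentage points against the planned 56. The 73 keeps 56 observed outcomes only while loss is at most (73 − 56)/73 = 23.3%. This shortfall arises because 56 was multiplied by 1.3; dividing by 0.7 gives 80. That is a separate matter from the analysis set.

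**4. Bias of a complete-case comparison.** In one arm, let p be the proportion lost and g the mean ASM change in completers minus that in drop-outs. The full-arm mean equals the completer mean minus p × g, so the completer mean is off by p × g. For the difference between arms:

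bias = p₁ × g₁ − p₂ × g₂

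- Equal loss and equal gaps in both arms: bias = 0.
- Loss of 40% and 20% with a common gap g (assumed, not in the documents): bias = 0.4g − 0.2g = 0.2g. This is 0 at g = 0 and 0.12 kg at g = 0.6 kg.

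The documents give neither the loss by arm nor the gap, so the formula shows what the bias depends on and does not estimate it.

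**The case against.** The strongest reply is that nothing in the article excludes drop-outs. ANCOVA after imputation can include everyone randomised, missing-data handling is commonly left to a full protocol or SAP, and inflating a sample for attrition is ordinary practice in an intention-to-treat trial. Most of this stands. Silence on imputation would not be a finding on its own, and the inflation to 73 does not contradict the intention-to-treat sentence, because missing outcomes cost information even when they are imputed. What remains is that the article itself commits to a set that its named methods cannot deliver at its own attrition allowance.

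Three stronger readings are tempting, and the documents do not support them.

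- *A completer analysis is what is planned.* A reader might infer this, but no such set is named. It is what results if only the named methods are applied.
- *Thirty per cent will have no scan.* The article gives an attrition rate, not a missing-scan rate. Someone who stops the diet may still attend at Week 12, so 22 is an upper figure under that allowance.
- *The result will be badly distorted.* Opposite gaps of 0.6 kg with 30% loss in each arm would give 0.3 × 0.6 + 0.3 × 0.6 = 0.36 kg, and setting drop-outs' change to zero would shrink 0.9 kg to 0.7 × 0.9 = 0.63 kg. The first rests on unsourced gaps in opposite directions. The second describes a carry-forward method that the article never proposes.

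**Conclusion.** The point holds as an inconsistency in the stated primary analysis. The promise to include everyone randomised cannot be kept by paired t-tests and ANCOVA alone once any Week 12 DXA is missing. Up to about 22 of 73 participants would be affected, leaving about 51 and roughly 75% power against the stated 80%. This assumes that all attrition means a missing scan, that allocation is 1:1 and that ±1.2 kg is an SD.

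Whether the resulting complete-case comparison would be biased, and by how much, is unknown. The bias is zero if drop-out rates and completer/drop-out gaps are the same in both arms. The same inconsistency applies to the other outcomes scheduled only at baseline and Week 12. It should be resolved before the data are analysed by arm, because the label and the validity of the primary result depend on it.

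**What to change.** 1. State that the scheduled Week 12 DXA will be sought from every randomised participant, including those who have stopped the diet. This reduces the problem at source.
2. Define the primary analysis as an ANCOVA of Week 12 ASM on diet group, with baseline ASM and BMI stratum as covariates, after multiple imputation of missing Week 12 ASM by arm. Naming these covariates replaces, for this model, the selection by correlation matrix.
3. Keep the imputation model small, since only about 25 outcomes per arm may be observed: baseline ASM, sex, BMI stratum and one summary of the fortnightly weights, such as the last observed value or the slope. The weights bring post-baseline information on drop-outs that a complete-case ANCOVA does not use.
4. Report complete-case and delta-adjusted analyses as sensitivity analyses.
5. If imputation is not adopted, describe the set as randomised participants with Week 12 data, and do not claim that all randomised participants are included.

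The cost is some extra analysis work; the fortnightly weights and the Week 12 visit are already planned. The primary analysis would rely on a missing-at-random assumption, and the delta-adjusted analysis shows how far the conclusion depends on it. Imputation should not be expected to restore the power of 73 observed outcomes.

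### A normality check on the variable, not on the model residuals, decides whether the primary ASM result is a kg difference, a ratio or a rank contrast, although the trial is powered on a kg difference

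*Protocol article*

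**What the plan says.** All of the rule stands in the protocol article under Power calculations, intention to treat and statistical analyses.

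- **The rule.** Of variables that are not normally distributed it says: "variables will be logarithmically transformed before analysis. Where normality is not achieved, non-parametric methods for analyses will be used". It covers every variable and makes no exception for the primary outcome. It gives no normality test, no threshold and no name for the non-parametric method.
- **The powered quantity.** "This study was powered on the primary outcome of change in ASM", with a target "change in ASM between the two study groups of 0.9 kg ± 1.2 kg".
- **The outcome as named elsewhere.** The Data collection section says only "The primary outcome measure for this study will be ASM", without saying whether this is change or the Week 12 value.
- **The between-group model.** ANCOVA is named, to be run after an assumption screen that includes normality. Covariates are to be picked from a correlation matrix. Baseline ASM is not listed among them.

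**The concern.** Three things do not fit together.

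1. **The check has the wrong target.** ANCOVA needs roughly normal residuals, not a normally distributed outcome variable. Table 1 does not restrict eligibility by sex, so pooled ASM is probably a mixture of a male and a female distribution. It can look non-normal when the model fits well.
2. **The result changes scale.** A log analysis of Week 12 ASM gives a ratio and a rank test gives a rank contrast. Neither is the 0.9 kg difference on which the sample size rests. The data, not the plan, would choose among them.
3. **The log step does not suit several outcomes.** Change in ASM during weight loss will often be zero or negative. IPAQ activity, the 0–100 SF-36 scales and the 0–12 SPPB can all be zero.

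The fallback also does not say whether covariate adjustment is kept. At stake are the meaning of the primary result and, on some readings, its power.

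**Working it through.** **The plan's own figure.** Inputs from the protocol: difference 0.9 kg, SD 1.2 kg (reading the ± as an SD), two-sided 0.05, power 80%. Equal allocation is assumed.

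n per arm = 2 × (1.960 + 0.842)² × (1.2 / 0.9)² = 2 × 7.85 × 1.778 = 27.9, so 28 per arm and 56 in total. The stated 56 is reproduced, and it belongs to a kg difference in change. With a t-test, power at 28 per arm is 0.787. Of 73 randomised with 30% attrition, 73 × 0.70 = 51.1, so 51 completers are used below.

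The documents give no ASM means or SDs, no proportion of men and no normality test. Everything from here rests on assumed values and on Shapiro–Wilk at 0.05.

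**Reading A: the outcome is change in ASM.**
- Assume a mean change of −1 kg with SD 1.2 kg. The share below zero is Φ(1 / 1.2) = Φ(0.83) = 0.80. Every simulated trial had at least one zero or negative change, so the log step cannot be carried out as written.
- The check fails in about 5% of trials if change is normal, and in 39–50% if it is heavy-tailed (t with 4 df).
- Power at 28 per arm with normal errors: Mann–Whitney on change 0.76, ANCOVA with baseline 0.78. With heavy tails: 0.89 against 0.79. At 51 completers with normal errors: 72.3% against 74.1%. The loss is about 2–3 points, or there is a gain.

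**Reading B: the outcome is Week 12 ASM.**
- Assume men 25 (SD 3.2) kg, women 17.5 (SD 2.4) kg, 30–50% men, n = 51 to 73.
- Raw ASM fails the check in 23–71% of trials, lowest at n = 51 with 50% men and highest at n = 73 with 30% men. ANCOVA residuals fail in about 5%. Raw and logged ASM both fail in 8–15%.
- The whole rule was run as: ANCOVA in kg with baseline if raw ASM passes; ANCOVA on logs if only the log passes; otherwise an unadjusted Mann–Whitney test. At n = 51 its power is about 68–70%, against 73–74% for ANCOVA throughout, a loss of about 4–6 points. A second run with the same inputs gave 68–69% against 74–76%, a loss of 6–7 points.
- With more separated distributions (men 27, SD 3.0; women 18.5, SD 2.2; 40% men; 28 per arm), raw ASM fails in about 67% of trials. The whole rule then has power 0.58 against 0.78, a loss of 20 points.

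**Worst case: an unadjusted rank test on Week 12 ASM in every trial.** Effective n per arm is 28 × 3/π = 26.7. Power = Φ(0.9 / (SD × √(2 / 26.7)) − 1.96).

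| Between-person SD (kg) | Power |
|---|---|
| 2 | 0.38 |
| 3 | 0.19 |
| 4 | 0.13 |
| 5 | 0.10 |

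**Type I error.** With no true difference, all methods stayed at 0.04–0.05.

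**The case against.** The case for leaving the rule alone has real content.

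- **An article condenses.** Which normality test and which rank method to use could be left to an analysis plan. That stands, and their absence is not the point. The rule itself is stated, and it reaches the primary outcome.
- **The screen before ANCOVA may look at residuals.** It may; the text does not say. But the transformation rule is worded for variables, and it acts before analysis.
- **Step two catches what the log cannot handle.** For IPAQ, SF-36 and SPPB this is largely true. The log step is then pointless rather than harmful.
- **A rank test on change costs little.** This stands, and with heavy tails it gains power.

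A reader might infer more than the text supports:

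- *That the fallback strips out baseline adjustment.* The method is unnamed, and a rank-based ANCOVA would fit the words. Nor does the protocol fix a baseline-adjusted model to begin with, since baseline ASM is never named as a covariate.
- *That the trial would have about 10% power.* That needs an unadjusted rank test on Week 12 ASM with a between-person SD near 5 kg.
- *That the undefined log and the power collapse occur together.* They do not. The first needs change as the outcome; the second needs Week 12 ASM, which is always positive.

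**Conclusion.** The point holds in a limited form. The protocol lets a data-dependent check on the variable choose the scale and method of the primary analysis, while the sample size rests on a kg difference in change. This is a stated rule that works badly, not a missing detail.

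The main harm is to what the primary result means. The effect on power is secondary and depends on the reading: about 2–3 points for a rank test on change; roughly 4–7 points for the whole rule on Week 12 ASM at 51 completers, and about 20 points under a more separated assumed distribution; power near 10% only in the worst case. The Week 12 figures assume that the ANCOVA includes baseline ASM and that the fallback is unadjusted, neither of which the protocol states. Nothing here shows an inflated type I error.

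**What to change.** Exempt the primary outcome from the rule and fix one analysis for it:

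- Analyse ASM in kg, untransformed, by one ANCOVA: Week 12 ASM on diet group, baseline ASM and the BMI stratum used at randomisation.
- Judge assumptions on the residuals of that model. If they are clearly skewed or heteroscedastic, report a bootstrap or heteroscedasticity-robust 95% confidence interval for the same adjusted kg difference.
- Keep log-scale and rank-based analyses of ASM as sensitivity analyses.
- For secondary outcomes that are bounded or can be zero (IPAQ, SF-36, SPPB), skip the log step and use a baseline-adjusted rank, ordinal or bootstrap method.

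The cost is wording and minor programming. The evaluable sample size stays at 56: simulated ANCOVA power at 28 per arm is 0.78–0.79, in line with the 0.787 that the t-test gives for the plan's own inputs.

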Manipulating dietary composition during energy intake restriction, in particular protein intake, may attenuate the loss of SMM and strength. To date, most geriatric obesity weight loss trials have adopted dietary strategies involving the manipulation of dietary protein to preserve lean tissue during energy intake restriction [19–26]. Dietary protein intake stimulates muscle protein synthesis (MPS) and facilitates postprandial muscle protein accretion [27, 28]. Despite earlier studies suggesting that a decline in basal MPS may contribute to skeletal muscle wasting in the elderly [29, 30]; it appears that the elderly may be less able to efficiently utilize amino acids for MPS, resulting in a blunted muscle protein synthetic response to an anabolic stimuli, a phenomenon termed anabolic resistance [27, 31]. As of consequence, evidence based recommendations for protein intake in older adults have recently been published [32, 33]. However, there are no specific recommendations for obese older adults during energy intake restriction. Weijs and Wolfe [20] recently showed that at least 1.2 g/kg body weight or 1.9 g/kg FFM as optimal daily protein intake for obese older adults during energy intake restriction. Despite this however, an important determinant of MPS is not only an adequate intake of dietary protein. Plasma levels of antioxidants, in particular carotenoids and polyphenols, have shown to be inversely associated with sarcopenic symptomology and frailty [34–38]. Similar observations have been observed for fruit and vegetable intake [39–42]. Furthermore, a number of observational studies have reported that greater adherence to a Mediterranean Diet, characterized by a high intake of carotenoids from fruits and vegetables and polyphenols from extra-virgin olive oil (EVOO), is associated with lower odds of sarcopenia, frailty and improved mobility and physical performance [43–51]. Vegetable intake, in particular green-leafy vegetables, has shown to be associated with increased levels of physical activity [52]. In addition, increases in plasma lutein through supplementation are correlated with increases in physical activity and reductions in sedentary time in older adults [53]. Thus, an increase in carotenoids may attenuate loss of SMM by increasing physical activity during dietary energy restriction. The efficacy of carotenoid rich fruits and vegetables plus EVOO when coupled with a high protein, energy restricted diet however is unknown.

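### The ANCOVA covariates are to be chosen from a correlation matrix, so the primary model is fixed neither in its terms nor in its dependent variable

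*Protocol article*

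**What the plan says.** All the analysis text is in the protocol article, under Power calculations, intention to treat and statistical analyses.

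- **Model.** ANCOVA is specified "with diet groups as the independent variable and outcome parameters as the dependent variable". No covariate is named.
- **Covariate rule.** "Covariates will be determined using a correlation matrix to identify significant interactions between potential confounders".
- **Outcome used for power.** "This study was powered on the primary outcome of change in ASM", with a difference of 0.9 kg, an SD of 1.2 kg and 56 evaluable participants.
- **Baseline comparison.** "independent sample t-tests or chi square analysis will be used to ensure that there are no significant differences between randomised groups".

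Three other places bear on the model:

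- Study design, participants and recruitment: "Allocation will be stratified by BMI", with strata 27–29.9 and ≥30 kg/m².
- Data collection: "Assessment of all outcome measures (primary or secondary) will be conducted at baseline and Week 12". Body weight and physical activity are among the secondary outcomes, so both have post-randomisation values.
- Background: "an increase in carotenoids may attenuate loss of SMM by increasing physical activity during dietary energy restriction".

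**The concern.** The rule cannot do what it says. A matrix of pairwise correlations shows linear association between pairs of variables and carries no information on interaction. The text also leaves open which correlations count (with the outcome, with diet group, or among the covariates) and which values enter. Two careful analysts could reach different primary models from the same data.

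The rationale is also misplaced. Randomisation deals with confounding by design. Covariates in a randomised comparison are chosen in advance because they are prognostic or were used to stratify allocation. The two obvious ones here, baseline ASM and the BMI stratum, are not fixed. The dependent variable is also unsettled: the power paragraph speaks of change, while the ANCOVA sentence speaks only of outcome parameters.

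At stake is the single primary comparison. If its covariates are settled after the data have been examined, nobody can show afterwards that the P value did not influence the choice.

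**Working it through.** **1. The plan's own figure.** Inputs from the power paragraph: difference 0.9 kg, SD 1.2 kg (reading ± as SD), two-sided 0.05, power 80%. Equal allocation is assumed.

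n per arm = 2 × (1.960 + 0.842)² × (1.2/0.9)² = 2 × 7.85 × 1.778 = 27.9, so 28 per arm and 56 in total. This reproduces the stated number. With the noncentral t, power at 28 per arm is 78.7%. The calculation is an unadjusted two-group comparison of change, with no covariates.

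**2. What the covariate rule does to that comparison.** The documents give no covariate correlations, so these are assumptions: 28 per arm, outcome SD 1.2 kg, eight baseline candidates of which four correlate about 0.2 with the outcome, selection at P < 0.05 on the correlation with the outcome, 4000 simulated trials per setting.

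| Analysis | Rejection rate, true difference 0 | Rejection rate, true difference 0.9 kg | Mean estimate, true difference 0.9 kg |
|---|---|---|---|
| No covariates | 5.2% | 79.1% | 0.90 kg |
| Covariates selected mechanically | 5.2% | 78.7% | 0.85 kg |
| Smallest P of 11 models | 10.3% | 88.3% | – |

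The 11 models are the unadjusted one, the mechanically selected one, eight with a single covariate, and one with all eight. Simulation error (1.96 × √[p(1−p)/4000]) is about ±0.7 percentage points at 5.2% and ±0.9 at 10.3%.

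On average 1.3 to 1.5 covariates were selected. The selected-model estimate differed from the unadjusted one with an SD of 0.12 to 0.13 kg. The standard error of the unadjusted difference is 1.2 × √(2/28) = 0.32 kg, so the choice of covariates moves the estimate by roughly 0.4 of a standard error (0.12/0.32 = 0.38; 0.13/0.32 = 0.41).

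**3. Does leaving baseline ASM unfixed cost power?** That depends on the unsettled dependent variable.

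- If change is analysed, almost nothing is lost. At 26 v 25 (about 30% loss from 73) power without baseline ASM is 74.7%, against about 74% in a simulation with it.
- If Week-12 ASM is analysed and baseline ASM is among the candidates, the matrix would select it. With an assumed 60% women and change SD 1.2 kg, the baseline to Week-12 correlation averaged 0.96 and was significant in all 4000 simulated trials.

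**4. Post-randomisation values.** Set side by side, the rule does not restrict candidates to baseline, physical activity is measured again at Week 12, and the Background offers it as a route to preserved muscle. If its change entered the model, the mediated part of the effect would be removed. The documents give no mediated share, so no size is put on this.

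**The case against.** The strongest reply is that the rule, applied as a rule, does little harm. With baseline candidates and mechanical selection, type I error stays near 5% and the mean estimate falls only from 0.90 to 0.85 kg. The 10% figure needs an analyst free to choose among models. This stands as a limit on the size. It does not remove the defect, because the text describes no mechanical procedure.

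A second reply is that an article may leave the covariate list to a fuller protocol or analysis plan. That is fair for an absent list, but here a selection rule is stated, and a later plan would have to contradict it.

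A reader might infer two stronger things, and the documents support neither.

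- *That power collapses because baseline ASM is omitted.* This needs a raw Week-12 outcome with baseline ASM neither fixed nor selected. The trial is powered on change, and the rule would itself pick up baseline ASM if offered it.
- *That the plan will adjust away the diet effect.* No passage says Week-12 or change values will be covariates. The rule speaks of confounders, which does not describe a mediator. Participants are asked to keep their habitual activity, and the Background says only that the pathway may operate. This is a gap to close, not a stated plan.

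Two related matters are minor. Omitting the stratum from a linear model does not bias the estimate and usually makes the standard error slightly conservative. The baseline tests cannot guarantee balance, but the text does not link them to covariate choice.

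**Conclusion.** The concern holds in a limited form and should be fixed. The plan determines the primary model's covariates by a data-driven rule that cannot do what it claims. It fixes neither baseline ASM nor the BMI stratum, and it leaves the dependent variable open between change and Week-12 ASM.

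Type I error ranges from about 5% under strictly mechanical selection of baseline covariates to about 10% under free choice among 11 models. Both figures rest on the assumed eight candidates, four correlated about 0.2 with the outcome, and 28 per arm; other assumptions would move the upper figure. The stated 56 evaluable participants are not called into question by this point. Mediator adjustment remains a caution only.

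**What to change.** Replace the covariate sentence, before outcome data are examined, with wording such as:

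> Primary analysis: ANCOVA of Week-12 ASM (kg) on diet group, baseline ASM and BMI stratum (27–29.9, ≥30 kg/m²). Each secondary outcome uses its own baseline value and BMI stratum. No variable measured after randomisation enters the primary model. Any other adjustment is exploratory.

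Report baseline characteristics descriptively and drop the significance tests between arms.

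The cost is wording and about 2 degrees of freedom (one each for baseline ASM and BMI stratum; 54 to 52 at 56 participants). All the variables are already collected, and the evaluable sample size need not change on this account.
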